#### Physical activity

Physical activity is objectively assessed using the Actical® (Minimitter, Oregon), which is a small, water-resistant, omni-directional accelerometer. This device is sensitive to low frequency movements in the range of 0.5–3.2 Hz, which is the common range for human movement. Participants are asked to wear this device on the right hip during the waking hours (at least 12 h) for 7 days. Participants record a daily log of their Actical use, including times when the device is removed or replaced, and times of significant physical activity. The Actical has been previously validated for use in the pediatric population and those with CHD [25, 26]. Self-reported physical activity is also assessed using the Physical Activity Questionnaire for Older Children (PAQ-C, Version 2, 2009) [27]. This is a nine-item, 7-day, recall questionnaire for older children that assesses general moderate-to-vigorous physical activity during the school year. The PAQ-C is previously validated for use in children aged 8–14 years [28]. Participants and parents are also asked if the parents have ever restricted the participant’s physical activity because of the heart condition.

#### Quality of life assessment

This study uses the Pediatric Quality of Life Inventory Generic Core Scales (PedsQL™, Version 4.0, ©1998 JW Varni) parent and child (8–12 years) or parent and teen (13–18 years) reports to evaluate physical and psychosocial (emotional, social, and school) functioning. PedsQL™ Generic Core Scales are previously validated for use in children with heart disease [29].

#### Assessment of muscle function

Mechanography is a relatively new tool for assessing muscle function in children. This study used the Leonardo Mechanograph® Ground Reaction Force Plate (Novotec Medical Inc., Pforzheim, Germany) and proprietary software (GRFP Research Edition® software, version 4.2-b05.53-RES.). The device is a quadratic platform divided into two sections that can measure the vertically applied forces from the right and left lower limbs separately (Fig. 3). Signals from the four plate sensors are recorded by a portable computer using a 2.0 USB connection. Depending on the test performed, the software captures force data and derives acceleration, power, energy, speed, and jumping height. Reference values have been generated for children and adolescents using the Leonardo Mechanograph® platform, and reproducibility has been ascertained in healthy populations of children [30].

**Fig. 3 Fig3:**
[figure not shown]
Eight-year-old boy performing a two-leg jump on the Leonardo Mechanograph® platform

#### Electrocardiographic measurements

A standard 12-lead ECG is obtained by a qualified technician on supine participants who have been resting in position for at least 5 min. The ECG markers measured and analyzed include criteria for left or right ventricular hypertrophy, heart rate, QRS duration, and PR and QT intervals.

#### Transthoracic echocardiographic measurements

Following a modified functional protocol based on the American Society of Echocardiography guidelines and using commercially available machines (Vivid S6 or Vivid 9, GE Medical Systems, Milwaukee, WI, USA), parasternal long axis, parasternal short axis, and apical 4, 2, and 3 chamber images are acquired to measure M-Mode, two-dimensional data are used to obtain left ventricular volumes, ejection fraction, and strain analysis, and Doppler and tissue Doppler are used to measure additional systolic and diastolic parameters, while participants are lying supine [31]. Left ventricular strain is analyzed off-line using a commercially available software analysis (EchoPac, Version 7.1, GE Medical Systems, Milwaukee, WI, USA), following published guidelines [32].

#### Endothelial function

Endothelial vasodilator function, as an indicator of the earliest signs of cardiovascular disease, is assessed using peripheral arterial tonometry with the Endo-PAT 2000 (Itamar Medical Ltd., Caesarea, Israel) [33]. The fasting participant lies supine without movement for 15 min while the reactive hyperemia index is measured by finger-tip plethysmography following occlusion of brachial artery blood flow for 5 min in one arm, compared to the non-occluded contra-lateral arm. The reactive hyperemia PAT index (RH-PAT) is then calculated using an automated algorithm. RH-PAT and log-transformed values for each participant at the three intervention time points are entered into a database for statistical analysis. A lower value is indicative of a greater degree of cardiovascular disease and other conditions associated with impaired endothelial function or cardiovascular disease risk. Dietary and exercise intervention can improve endothelial dysfunction in obese children [34].

#### Laboratory measurements

Blood is drawn from patients who have been asked to fast for at least 10 h. The blood work includes lipid profile, electrolytes, creatinine, urea, fasting glucose, A1C, serum insulin, and adiponectin, a serum protein inversely associated with metabolic syndrome and insulin resistance [35]. In collaboration with the Translational Research Centre, the serum is stored in repository at − 85 °C until further analysis.

#### Participant feedback

When exiting the study, participants, and their accompanying parent or caregiver, are asked to complete a program evaluation form with ratings and comments on the life coaches, the technology, and the participant experience, including suggestions for improving the intervention program. Comments and scores for each question of the evaluation form are entered into a database. Anonymous metadata are used by staff and investigators for continuous quality improvement and decision-making. This qualitative information is also valuable for evaluating the research program from a participant and family perspective.

### Sample size for the pilot and feasibility study and statistical analyses

A relatively small sample size (*n* = 40) was selected to test the feasibility of the intervention. A power calculation was not used as we were unable to determine the variability and expected difference in our primary outcome measures for our study population. As such, the results from the current study will provide the required information to perform power calculations for future studies.

The mean, SD, 80% confidence intervals, and 95% confidence intervals (95% CI) will be calculated and reported for all ratio and interval-based outcome measures, for each of the three time points and overall. The following hypothesis testing will also be performed, but purely as an exploratory exercise and as a component of the pilot. Temporal changes in primary and secondary outcome measures will be assessed using a repeated measures analysis of variance. Specifically, data will be analyzed using analysis of variance (ANOVA) and covariance (ACNOVA) with Bonferroni post hoc comparisons with IBM SPSS Statistics for Windows, version 24 (IBM, USA). Participants with missing data may be excluded from analysis if relevant. These data will be critical for informing future large-scale, controlled trials and establishing variances for the outcome metrics for sample size calculations.

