## Background

Both obesity and congenital heart disease (CHD) are important risk factors for the long-term cardiovascular health of children and adolescents. With an overall incidence of approximately 1% of live births, CHD ranks among the most common birth diseases [1]. Moreover, the prevalence of CHD in older populations is on the rise, and health professionals must increasingly manage CHD in the context of complex, acquired health conditions [2, 3]. Currently, about one third of children in Canada and the USA are overweight or obese [4], and research suggests that the prevalence of overweight and obesity between CHD children and healthy children does not differ significantly [5, 6].

The numerous cardiovascular risks and physical and psychosocial health consequences of childhood obesity are well reviewed [7, 8]. Of particular relevance to this paper are the accelerated atherosclerosis, endothelial dysfunction, cardiovascular structural abnormalities, dyslipidemia, insulin resistance, and hypertension. While evidence is only emerging, children with CHD and weight problems appear more likely to exhibit additional cardiovascular risk factors compared to normal weight controls [5, 9]. This is of great concern considering the increasing prevalence of metabolic syndrome in children and adolescents [10, 11].

Changes in nutrition and physical activity, including sedentary behavior, can impact both weight status and cardiovascular disease risk [12]. A structured lifestyle intervention for overweight and obese children with CHD has the potential to diminish cardiovascular health and metabolic syndrome risk factors by improving nutrition, physical fitness, body composition, and related health outcomes. However, conventional pediatric lifestyle intervention programs struggle with barriers to their success, such as high attrition rates and therapeutic non-compliance [13].

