Feasibility of the study will be assessed by evaluating the protocol in several different areas. The integrity of the study protocol will be examined to determine the adequacy of the inclusion/exclusion criteria, to make sure all equipment is functional and provide the desired outcome data, and staff are properly trained to administer and assess the intervention as well as the overall logistics and flow of the protocol. Recruitment and consent will be evaluated based on the consent rate and any barriers identified. The intervention will be assessed for acceptability by the participants based on participation levels, compliance, and retention. The results from self-reports and questionnaires will be evaluated to determine patient compliance and assess the specific questions for comprehension by the participants as well as their suitability to provide the required data for evaluation. Several primary and secondary outcome measures are included in the pilot study, and specific metrics will be evaluated for reliability and feasibility to determine which are the most appropriate for evaluation of the intervention. These metrics will also be used for sample size estimations as required for performing a larger study.

The primary outcome measures for the pilot study are anthropometry, body composition, and cardiorespiratory exercise capacity. The secondary metrics include nutrition and physical activity outcomes, quality of life, cardiovascular and muscle function, and biochemical risk markers. Outcomes are assessed at baseline, 6 months, and 1 year at the Children’s Hospital, LHSC, and the Western University (UWO). These outcome measures will be exploratory.

This study is approved by the Western University Health Science Research Ethics Board (REB# 18843). Recruitment for the study was initiated in February 2013 and is currently ongoing. The Standard Protocol Items: Recommendations for Interventional Trials (SPIRIT) checklist for the Smart Heart study can be found in Additional file 1: Table S1. The schedule of enrolment, interventions, and assessments for the Smart Heart study can be found in Fig. 1.

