### Feasibility outcomes

#### Integrity of the study protocol

The number of patients eligible to participate in the study based on the exclusion and inclusion criteria will be used for evaluation. If fewer than 10 patients are eligible per month, the exclusion/inclusion criteria will be re-examined and/or the time frame for recruitment adjusted for future studies. A complete run through of the protocol will identify any critical unforeseen issues with equipment, data collection, metrics used, timing, scheduling, training, and procedures. Adjustments to the protocol logistics and/or processes will be made where appropriate so the protocol is efficient and appropriate to meet the goals of the study. Feedback elicited from the research assistants, nutritionist, fitness specialists, and participants will be used for evaluation. All instruments/protocols used for data collection will be required to collect acceptable data from ≥ 80% of the study participants.

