#### Acceptability of the intervention

The intervention will be evaluated for acceptability through assessment of patient participation, compliance, and retention. These metrics will be obtained from the patients’ weekly reports, attendance records, level of engagement with the dietician and fitness specialist (i.e., missed and/or rescheduled appointments, length of the telephone conversations), and the retention rate. A minimal retention rate of ≥ 70% with ≥ 80% compliance would be acceptable.

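### The open-ended exclusion rule, combined with repeated-measures ANOVA, permits a complete-case analysis of change chosen after the data are seen; it discards observed visits and can bias the change estimates in a direction the protocol does not establish

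*Protocol article*

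**What the plan says.** In the section on sample size and statistical analyses, the protocol article states: "Temporal changes in primary and secondary outcome measures will be assessed using a repeated measures analysis of variance". It names ANOVA and ANCOVA with Bonferroni comparisons in SPSS. Missing data get one sentence: "Participants with missing data may be excluded from analysis if relevant". The section does not define when exclusion is relevant or say when this is decided. It names no method that keeps incomplete children and no sensitivity analysis.

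The same section treats the hypothesis tests as exploratory. As a separate step, it plans means, SDs and 80% and 95% confidence intervals at each of the three visits. It also says the results are to inform later controlled trials and their sample sizes.

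Two other places show that missing data were foreseen. The Background says conventional programmes of this kind "struggle with barriers to their success, such as high attrition rates and therapeutic non-compliance". Under Acceptability of the intervention: "A minimal retention rate of ≥ 70% with ≥ 80% compliance would be acceptable". Against this, the Discussion describes completion in this study as high, without a figure.

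**The concern.** A repeated-measures ANOVA over three visits conventionally drops a child from an outcome when any one value is missing. The exclusion sentence allows that outcome and leaves the choice open until the data are in hand. Two things follow. Baseline and 6-month values that families and staff worked to obtain would go unused in the analysis of change. The estimated change would also describe only children who stayed, and if staying is related to progress, it would not describe the children who were enrolled.

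This is more than detail left to an analysis plan. The article fixes both the method and the rule, and the rule has no content that would limit it. At stake are the change estimates, which a later team would naturally read as the signal for a controlled trial.

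**Working it through.** **Inputs from the protocol article.** Planned n = 40, chosen without a power calculation, so there is no stated figure to reproduce. Retention floor 70%. Three visits. The future trial is to be sized from the 80% upper confidence limit of the SD.

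**1. Visits discarded at the floor.** 40 × 0.70 = 28 children complete and 12 are lost.
- All 12 leave after month 6: collected visits 28 × 3 + 12 × 2 = 108; used 28 × 3 = 84; discarded 24.
- All 12 leave after baseline: collected 28 × 3 + 12 = 96; used 84; discarded 12.

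**2. Precision.** The 95% CI half-width for a mean, in SD units, is t(0.975, n − 1)/√n.
- n = 40: 0.320
- n = 28: 0.388

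If the 12 children leave after month 6, all 40 have a 0–6 month change. For that contrast the loss from 0.32 to 0.39 SD is wholly avoidable. For the 0–12 month change, an all-data analysis would fall roughly between the two, depending on how strongly the 6- and 12-month changes correlate.

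**3. Effect on the SD carried forward.** The factor is √[(n − 1)/χ²(0.20, n − 1)]: 1.114 at n = 40 and 1.142 at n = 28. Sample size scales with its square: 1.304/1.240 = 1.05, so about 5% more children. On this count alone, the smaller n makes the next trial slightly larger.

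**4. Bias in the 12-month change.** This needs assumptions that the document does not supply. A simulation used 4,000 replicates of n = 40, true change zero, between-visit correlation r = 0.9, and an average 30% loss before month 12. Dropout was logistic with the stated log-odds slope per SD of change. Bias is in SDs of change; negative means toward benefit for a measure where an increase is worse. The completer test was of the 12-month change among those remaining. The all-data estimate was the likelihood estimate using every observed visit.

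| Dropout driven by | Slope | Completers | All data | False positives, completers |
|---|---|---|---|---|
| nothing | 0 | 0.00 | 0.00 | 5% |
| observed 6-month change | 0.5 | −0.07 | 0.00 | 6% |
| observed 6-month change | 1 | −0.13 | 0.00 | 10% |
| observed 6-month change | 2 | −0.19 | 0.00 | 17% |
| observed 6-month change, better-doing children leave | −1 | +0.13 | 0.00 | 10% |
| unobserved 12-month change | 0.5 | −0.14 | −0.11 | 12% |
| unobserved 12-month change | 1 | −0.26 | −0.20 | 29% |
| unobserved 12-month change | 2 | −0.37 | −0.30 | 62% |

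With equal correlation r, the 6- and 12-month changes correlate at (1 − r)/[2(1 − r)] = 0.5 whatever r is. When dropout depends on the observed 6-month change, completer bias is proportional to that correlation. At 0.7 instead of 0.5, the first two biases become 0.073 × 1.4 = 0.10 and 0.125 × 1.4 = 0.175, and the third 0.189 × 1.4 = 0.26. A separate simulation at 0.7 gave 0.10 and 0.17 to 0.18 for the first two.

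**The case against.** The case on the other side is substantial, and most of it limits the size of the point.

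- **Direction.** A reader might infer that the analysis biases change toward benefit. The Background names attrition and non-compliance as barriers but does not link them to lack of progress, and nothing says who leaves. Zero or reversed bias is possible. This stands.
- **30% loss.** It is the edge of a feasibility criterion, not a forecast, and the Discussion describes high completion. This stands; the figures above are for the floor.
- **Smaller samples still.** Under Integrity of the study protocol: "All instruments/protocols used for data collection will be required to collect acceptable data from ≥ 80% of the study participants". A reader might multiply this by retention, once or per visit. The text does not state it per visit or among retained children. Even one multiplication, 28 × 0.8 = 22.4 of 40 or 56%, would fail the 80% threshold, so it cannot be the accepted scenario.
- **All summaries affected.** A reader might infer that every mean and SD would describe completers only. The per-visit summaries are a separate step and can use every available value, and the exclusion sentence permits rather than requires exclusion. The exposure is to the change estimates.
- **ANCOVA.** A reader might infer that an uncentred covariate would distort the test of time. No covariate is named, and a covariate in a one-arm repeated-measures model is not an error in itself. The document does not support this complaint.
- **Exploratory status.** The tests decide nothing; the thresholds that do are feasibility metrics. The assumed bias of 0.07 to 0.19 SD is also smaller than the 0.39 SD half-width. This lowers the severity but does not justify a rule without a criterion, because the results are meant to inform the next trial.

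**Conclusion.** The point holds for the analysis of change. The method and the exclusion sentence together permit a complete-case analysis that can be chosen after the data are seen. At the 70% retention floor, it would leave up to 24 of 108 collected visits unused and give a half-width of 0.39 rather than 0.32 SD. Under the dropout models assumed here (30% loss, log-odds slopes 0.5 to 2 on the observed 6-month change, correlation 0.5 between changes), it would shift the 12-month change by 0.07 to 0.19 SD toward benefit. The size grows with the correlation, and the sign depends on who leaves, which the document does not report. An all-data likelihood analysis removes the bias only when dropout depends on observed values; otherwise it reduces it. Because the tests are exploratory, this is a worthwhile correction rather than one that must be made before the study can be relied on.

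**What to change.** Delete the sentence allowing exclusion and replace the repeated-measures ANOVA with a linear mixed model for repeated measures: visit as a categorical factor, unstructured covariance, REML, fitted with SPSS MIXED. Include every child with a baseline value and all observed visits. Report the 0–6 and 0–12 month changes with 95% confidence intervals.

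Report, by visit and outcome, the number lost and their baseline features. Keep the completer analysis as a sensitivity analysis. Add one for dropout that depends on unobserved outcomes, for example by shifting the missing 12-month values in the unfavourable direction over a pre-stated range.

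The cost is a change of wording plus slightly more analysis and model output to explain. The software is the same and no new data are needed.

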## Discussion

In summary, this article has provided a rationale for the development of the intervention and an explanation of its study design and methods. This article has presented all of the information needed to develop and deliver a similar lifestyle intervention program, including making use of mobile technology as well as the study design, intervention components, and recruitment and measurement procedures. Although this feasibility study is ongoing, with an estimated completion date of the end of 2017, anecdotal reports from children and parents have been largely positive.

Despite the high completion rates, owing to the minimal burden on participating families, the following challenges were identified for future consideration of similarly designed studies: study compliance, technology, and measuring fitness and nutrition behavior.

The study is designed to mitigate certain potential compliance issues. First, adherence to the weekly telephone sessions may be challenging. For this reason, participants receive reminder text messages prior to their scheduled appointment times, which are rescheduled when necessary. The online supporting software may also be underutilized. To minimize this, participants are provided with in-person instruction on the software and are reminded to use the software through text messages and during counseling sessions.

The development of the online software required significantly more time than was originally planned, due, in part, to privacy reviews requested by the institutional REB. Researchers should temporally budget for software development and include respective institutional and governing research bodies early in the design process.

Quantifying physical activity is difficult because it is a multidimensional behavior; calculating the intensity, duration, frequency, and type with an all-encompassing tool is a challenge. Thus, accelerometers were chosen as an objective method of characterizing physical activity for this research project. Similarly, a variety of subjective and objective methods exist to characterize nutrition behavior. In this case, 3-day food records were chosen as the best approach to collect a variety of information about current participant intake and eating habits (e.g., timing of eating episodes, portion sizes, breakfast habits), which is useful for immediate interpretation by the registered dietitian in providing ongoing guidance to participants, with minimal participant burden.

A specific strategy for obesity management among pediatric cardiology patients, such as nutrition and physical activity guidelines and/or programs for at-risk patients, is lacking. The results from this pilot study will be made available with the intention to further knowledge in the management of pediatric obesity in CHD patients and in the application of smart mobile technology to pediatric health care programs in general. In the meantime, it is anticipated that the matters discussed in this article will inform researchers and health professionals developing related trials and programs.

